### Eligibility criteria

Hospital level

1. consent from the Hospital Management to participate to the study

Ward level

Including criteria

1. consent from the head of the ward to participate in the study;

2. ward classified as oncology, medicine, respiratory disease ward according to the regional classification of hospitals;

3. number of beds;

4. number of ordinary admissions with primary or secondary diagnosis of tumour (ICD-IX 140-239) >180 per year;

5. yearly average stay in hospital between 4 and 19 days;

6. punctual prevalence of patients with primary or secondary diagnosis of tumour (ICD-IX 140-239) ≥ 8 patients.

Excluding criteria

1. the ward had received or is receiving quality improvement programmes of staff education for improving pain control.

Staff level

1. affiliation to the ward;

2. informed consent to participate in the study.

Patient level

Including criteria

1. patients admitted in the ward for at least 24 hours;

2. age ≥ 18 years

3. able to fill in the questionnaire according the health care professionals judgment;

4. informed consent to participate to the study.

Excluding criteria

1 patient already assessed in one of the previous assessments.

### THE PAC-IFicO programme

In all selected wards the PAC-IFicO programme will be implemented. The **PAC-IFicO** programme shows significant differences if compared to previous Italian “Pain-free Hospital” experiences. Such differences can be listed as follows:

➣ a rigorous research in terms of methods and subsequent phases of the project;

➣ the use within hospital units of a “Program” with the same modalities of implementation;

➣ comprehensive employment of all the components of the “Program”;

➣ training based on adult education programs: education based on local barrier clearing (pre-education focus) and *peer-to-peer* training among colleagues;

➣ local organizational support interventions following the training phase;

➣ the involvement of both clinicians and nurses into the project [47];

Additional file 1: Table S1 describes the 4 phases of the **Pac-IFicO** Protocol [48,49].

Within each involved units, two Guides (a physician and a nurse) will be appointed, who will attend a four-day training course, with the aim to be enabled, in turn, to train and educate their colleagues in their unit relating to the “standard implementation” of the Program.

All the patients in the involved units will receive an information pack on pain control, during the whole protocol (three months after the completion of the training course for the health professionals).

After the training course for all the health professionals, the following organizational support interventions will be performed:

1. Monthly debate (for three months) on a **crucial clinical case** within the unit with the support of both the appointed Guides and a regional coordinator;

2. Peer to peer learning interviews among the unit staff with the Guides

3. Audit interview to the nurse coordinator of the unit three months after the completion of the training phase.

The Program includes a procedure for the evaluation of the quality of the implementation process. In particular, the following evaluations will be carried out:

➣ Evaluation of the training program; the whole process of design, implementation and learning assessment will be evaluated according to the Quality Improvement Programs. Process indicators will be used concerning the subsequent phases of both the training program for the Guides and of the standard implementation process.

➣ Evaluation of the organizational support program: all the critical clinical cases discussed within the unit will be analysed; all the support interviews among colleagues will be tracked and collected; all the audit interviews to the nurse coordinator and to the unit chief will be also analysed.

### Ethical approval

The protocol was approved by the Ethics Committee of the Promoting Center, **(CE 11/11, 18 febbraio 2011)**, and from the Ethics committees of all participating centres.

### Statistical considerations

#### *Primary end-point*

The primary outcome measurement in the present study is the percentage of hospitalized cancer patients with severe pain within the latest 24 hours (score 7-10).

### Sample size

To address the effectiveness of the Pac-Ifico Programme, a clustered sample size was estimated with an alpha error of 0.05 and a power of 80%, assuming an intraclass correlation coefficient (ICC) for the primary endpoint equal to 0.01. According to these assumptions we estimated that 10 hospital wards, with cluster size equal to 25 pre-intervention and 25 post-intervention patients corresponding to overall 500 patients, would be sufficient to detect an absolute decrease in the primary endpoint from 20% to 9%, corresponding to an odds ratio of 0.4.

### Statistical analysis

Patients’ characteristics by pre and post-intervention groups and/or by centres were reported as means, frequency and percentage, for continuous and categorical variables, respectively. Student t-test for continuous variables and Pearson chi-square for categorical variables were used to compare pre-intervention vs. post-intervention group.

To account for the nested nature of the study design (i.e. patients clustered within wards), primary and secondary endpoints were analysed with a generalized hierarchical linear model [50,51].

Results comparing pre-intervention vs. post-intervention group were expressed in terms of mean differences and odds ratios (OR) along with their 95% confidence intervals (95% CI) for hierarchical linear and logistic models, respectively. Some analyses were adjusted for known confounders as reported in details in the specific tables.

Two-sided P-values < 0.05 were considered statistically significant. All the analyses were performed using the SAS Statistical Package Release 9.1 (SAS Institute, Cary, NC, USA).

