## Methods/design

### Objectives

#### *Primary aim*

The primary aim of this trial is to evaluate the effectiveness of the Pac-IFicO programme in improving the control of severe pain in cancer patients admitted to general medicine, oncology and respiratory disease wards of three Italian regions.

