### Procedures of the study

#### *Identification of the wards*

The three regional coordinators of the study obtained from local health authorities the list of all hospitals and wards of the region. For each ward the following information was collected: denomination and classification, number of beds, number of ordinary admissions per year with a primary or secondary diagnosis of tumour (ICD-IX 140-239) and their average length of stay in ward. An approximation of the punctual prevalence of the oncological patients was estimated for each ward from the last two information.

The process of identification of the eligible wards participating to this study is performed according to the following procedures:

➣ identification of all potential eligible units from the list of the hospital wards of each region (criteria 2-6 of the ward-level inclusion criteria);

➣ phone interview with the nurse coordinators on previous training on pain management received by the wards (criteria 1 of the ward-level exclusion criteria);

➣ random sampling, for each region, of the first eligible ward and subsequent evaluation of the consent from the Hospital management and the head of the ward to participate in the study. The procedure were repeated until two eligible units per region were identified.

The procedures and the dimensions of assessment for each identified ward include three levels:

Ward level

○ Information about the total consumption of opioids of the ward in the 6 months before and in the 6 months after the implementation of the Pac-IFicO programme were collected from the Hospital pharmacy.

Staff level

○ For all physicians and nurses of the ward information about qualification, years of service, training in pain management were collected.

○ Knowledge of the ward professionals in pain management were assessed before and after the implementation of the intervention by administering the Italian version of the Pain Attitudes and Knowledge Scale (PAK) [24,42];

Patient level

○ The quality of pain management is assessed before and after the implementation of the intervention by administering the APS-POK [43] to all eligible cancer patients in five weekly established sessions. The first session will be before T0) and thereafter one week apart: T7-T14-T21-T28. Each session will start at 14.00 on a midweek day. Eligible patients of each ward were identified by the nurse coordinator in the morning of the established day of assessment.

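### The primary analysis names only clustering of patients within wards; if it is fitted with a ward intercept alone, the interval for the before-after odds ratio will be too narrow wherever wards change differently.

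*Protocol article*

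**What the plan says.** The Statistical analysis section explains the choice of model by one level of nesting: "patients clustered within wards), primary and secondary endpoints were analysed with a generalized hierarchical linear model". The before-after comparison of a binary endpoint is reported as an odds ratio with a 95% confidence interval, and "Two-sided P-values < 0.05 were considered statistically significant". The section lists no random terms. It does not say whether the before-after change may differ by ward, or which degrees of freedom are used.

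The Sample size section works "with an alpha error of 0.05 and a power of 80"%, "assuming an intraclass correlation coefficient (ICC) for the primary endpoint equal to 0.01". It plans "10 hospital wards, with cluster size equal to 25 pre-intervention and 25 post-intervention patients corresponding to overall 500 patients", to "detect an absolute decrease in the primary endpoint from 20% to 9%, corresponding to an odds ratio of 0.4". It gives no separate figure for the correlation between the two periods in a ward.

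Under Eligibility criteria, a patient who has already been assessed is excluded, so the two periods are different patients from the same wards.

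The number of wards is not consistent. The Abstract and the Sample size section say ten. Identification of the wards says "The procedure were repeated until two eligible units per region were identified", and the Primary aim covers patients "admitted to general medicine, oncology and respiratory disease wards of three Italian regions". Two wards in each of three regions make six.

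**The concern.** The programme is delivered to wards, and its effect is measured as a change within each ward. A ward that always has more severe pain than another raises both its before and its after figure, so that difference does little harm to the contrast. The harmful variation is in the change itself: some wards improve more than others, and each drifts in its own way between two short assessment windows.

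The article gives reasons to expect such variation. The programme is built around obstacles identified locally, each ward's own two Guides train their colleagues, and the wards are of three types in three regions.

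The named nesting has no place for this variation. If the model is fitted as that nesting reads, the standard error of the odds ratio reflects only patient-level noise around a common change. The study is uncontrolled, so the primary claim rests on this one contrast and its interval.

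**Working it through.** **Inputs from the article.** Severe pain 20% before and 9% after; two-sided 0.05; 80% power; intraclass correlation (ICC) 0.01; 25 patients per ward and period; ten wards (Abstract, Sample size), or six (two per region in three regions).

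**Assumed, because the documents do not give it.** The between-period correlation of ward effects, *c*, is taken from 1 (all wards change alike) to 0 (the two periods of a ward share nothing). An ICC of 0.05 is an illustration, five times the planned value.

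**1. The plan's own figure.** Without clustering and without continuity correction:

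n per period = [1.96·√(2·0.145·0.855) + 0.8416·√(0.20·0.80 + 0.09·0.91)]² / 0.11² = 159.7, or 160.

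Treating all 50 patients of a ward as one cluster, the design effect is 1 + 49 × 0.01 = 1.49. Then 160 × 1.49 = 238.4 per period, and 238.4/25 = 9.5 wards, rounded up to 10, gives 500 patients. Power at 250/1.49 effective patients per period is 81.9%. The stated 500 reproduces.

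**2. How much too narrow a ward-intercept interval would be.** The true design effect of the within-ward contrast is 1 + 24·ICC − 25·ICC·*c*. A ward-intercept model assumes *c* = 1, for which this equals 1 − ICC. The ratio of true to reported standard error is

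r = √[(1 + 24·ICC − 25·ICC·*c*)/(1 − ICC)],

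and the actual type I error of a nominal 5% test is 2·[1 − Φ(1.96/r)].

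| ICC | *c* | design effect | r | type I error | coverage of the 95% interval |
|---|---|---|---|---|---|
| 0.01 (planned) | 1 | 0.99 | 1.00 | 5.0% | 95.0% |
| 0.01 | 0.8 | 1.04 | 1.02 | 5.6% | 94.4% |
| 0.01 | 0.5 | 1.115 | 1.06 | 6.5% | 93.5% |
| 0.01 | 0 | 1.24 | 1.12 | 8.0% | 92.0% |
| 0.05 (assumed) | 1 | 0.95 | 1.00 | 5.0% | 95.0% |
| 0.05 | 0.8 | 1.20 | 1.12 | 8.1% | 91.9% |
| 0.05 | 0.5 | 1.575 | 1.29 | 12.8% | 87.2% |
| 0.05 | 0 | 2.20 | 1.52 | 19.8% | 80.2% |

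The number of wards does not enter r.

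**3. Simulation check.** A random-intercept logistic model with Wald intervals was fitted to data with no programme effect (20% in both periods, 25 + 25 patients per ward, 600 runs per setting). The standard deviation of the ward-specific log odds ratio was varied.

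| SD of ward change | type I error, 6 wards | type I error, 10 wards |
|---|---|---|
| 0 | 5.2% | 5.0% |
| 0.25 | 6.8% | 5.5% |
| 0.5 | 11.8% | 10.2% |
| 0.75 | 18.8% | 21.3% |

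For scale, the target effect is ln 0.4 = −0.92, so an SD of 0.5 is about half of it. A paired t-test on the ward differences stayed between 4.0% and 5.7% throughout.

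**4. Power of a test that allows for the variation.** At ICC 0.01 and *c* = 0, the variance of one ward's difference is (0.16 + 0.0819) × 1.24/25 = 0.0120.

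- Ten wards: standard error √(0.0120/10) = 0.0346, noncentrality 0.11/0.0346 = 3.18, critical t on 9 df 2.26, power 81%.
- Six wards: standard error √(0.0120/6) = 0.0447, noncentrality 2.46, critical t on 5 df 2.57, power 51%.

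**The case against.** The strongest reply is that the article does not specify an intercept-only model. A hierarchical model may carry a random period effect, and the remark about nesting may only explain why such a model was chosen. The exact random terms are often left to an analysis plan, which is not shown. This stands as a limit: a reader might infer that the plan excludes ward-specific change, but the text does not say so. It does not remove the point, because the article goes beyond naming a model class and states the nesting the model is there to handle. For a before-after contrast within wards, that is not the level that matters most.

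Three further inferences are tempting and are not supported.

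- **That few wards by themselves narrow the interval.** With no variation in ward change, six and ten wards both gave about 5% type I error. The small number matters for the reference distribution once change does vary.
- **That an error rate of 14% or 19% follows from the plan.** Such figures need an ICC of 0.03 or 0.05. At the plan's own 0.01, the worst case is 8.0%, and that puts all the correlation at ward-period level.
- **That the sample size already assumed ward-by-period variation and the analysis then dropped it.** The 500 reproduces with the conventional factor of 1.49. The ward-period factor of 1.24 gives 160 × 1.24 × 2 = 397. The sizing looks like ordinary cluster inflation.

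It is also fair to say that a random ward-by-period variance is hard to estimate from six to ten wards with few events each (25 × 0.20 = 5 before and 25 × 0.09 = 2.25 after). This is why the fix needs a fallback.

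**Conclusion.** The concern holds conditionally. Read as a ward-intercept model, the stated analysis understates the uncertainty of the primary odds ratio wherever wards change by different amounts, which is plausible for this programme. At the planned ICC of 0.01 the effect is modest, with type I error between 5.0% and 8.0%. It becomes material only with larger variation: up to about 20% at an assumed ICC of 0.05, or 10% to 12% if ward log odds ratios have an SD of 0.5. If all wards change alike, the interval is right. The documents do not give the quantity that decides between these cases, so these sizes are a range and not an estimate for this trial.

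**What to change.** State the primary model in full: logistic, with a fixed period effect, a random ward intercept and a random ward-by-period term. Test the period effect on wards-minus-1 degrees of freedom (9 for ten wards, 5 for six). Report a paired t-test on the ward-specific differences in proportion as the check, and name it in advance as the fallback if the ward-by-period variance cannot be estimated.

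Reconcile the ward count between the Abstract and Sample size (ten) and Identification of the wards (two per region), and restate the power for the number actually enrolled.

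The cost is analysis wording and a somewhat wider interval. With ten wards the planned 80% survives (about 81% at ICC 0.01 with zero between-period correlation). With six it does not (about 51% on the same assumptions), and wording alone cannot repair that.

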## Discussion

Although pain evaluation and management is codified both in available guidelines and, in Italy, also in the Law 38/2010, pain is still often uncontrolled both in cancer patients and in patients with non oncological chronic diseases.

Our Study aims to improve the quality of pain management in patients admitted to medicine, oncology and pneumology units in three Italian Regions: Liguria, Piemonte and Veneto.

By means of consolidated educational and organizational methodologies, the Pac-IFicO Programme actually reinforces current strategies for cancer related pain control according to international guidelines in some medicine, oncology and respiratory disease wards. Not only does the present study aim to consolidate scientific knowledge relating to clinical and non clinical recommendations contained in the object Program, but it also aims to assess the effectiveness of the whole Program as a tool to improve health care in cancer patients in pain.

The aim of this study was to assess whether the implementation of the programme may determine effective changes in the attitudes and behaviour of health professionals in view of a better practice, and whether these changes have a positive impact on the control of pain in cancer patients. The results will be analysed and interpreted at three levels: the ward level, the staff level, and the patient level, the last to evaluate the effectiveness of the induced changes in terms of an improved quality of health care.

One of the most innovative features of the present programme is the appointment of two Guides in the unit (a physician and a nurse, i.e. a small team) who will first attend a 4-day long training course, after which they will reproduce a “standard implementation” training to all their colleagues, including all the physicians and nurses within the involved unit. The hospital staff will thus become a source of continuous training, which multiplies by involving new professionals. Moreover, the monthly grand rounds on critical clinical cases, along with the peer to peer learning assessment interviews among the unit health professionals with the Guides strengthen and improve any educational initiative by including the whole involved staff.
